#### Methods to protect against other sources of bias

By randomising at the level of participant rather than by practice, there is a slight risk of contamination by communication between patients at the same practice allocated to different conditions. While we consider this risk to be low, the following measures reduce the risk further: identify potential participants who live in the same household and ensure that only one person from the same household receives a screening questionnaire; monitor attendance at the taster sessions, to ensure that anyone attending who has not received an invitation is recorded and checked against participants in the Control group; measure the amount of contamination at follow-up by: (i) asking participants whether they have attended a taster session, and if not, whether they personally know or have spoken to anyone else who has been invited to the NHS stop smoking services; and (ii) validation of self-report by keeping a record of attendance at the taster sessions.

It is not possible to blind participants to the receipt of a personally tailored letter, and invitation to a taster session. While the personal letter is generated in the practice by Research Assistants, the remainder of the research team in all cases are blind to the allocation of the participant, which will be enforced by the data management. In follow-up interviews, the interviewer will be blinded to the allocation of the respondent in order to avoid bias in outcome assessment.

External validity of the sample is estimated by comparing data on non-responders to the invitation to participate with that of responders. Data are anonymised by removing names, addresses, and NHS numbers of non-responders from the database. Gender, date of birth (converted to age), and postcode (converted to an IMD score via GeoConvert) are used to calculate means within each practice and compare to those of responders.

#### Duration of treatment period and follow-up

The process from the searching of records to identify smokers to the completion of the follow-up takes approximately 38 weeks. Recruitment takes place over 7 weeks, with three practice visits by members of the research team to process responses. Four taster sessions are held in each area, three to coincide with the visits to process responses, and a final one to which all remaining non-attenders are invited. Figure 1 shows detail of the timing of assessments, intervention, and follow-up.

**Figure 1 F1:**
[figure not shown]
Timing of assessments, intervention, and follow-up.

### Measures

#### Baseline measures

Lichtenstein [7] found that readiness, motivation, and dependence were positively related to follow through, readiness defined as smokers planning to quit in the next 6 months. The baseline screening questionnaire therefore uses the definitions and measures of motivation and readiness used by Lichtenstein [7] in order to provide the right encouragement to those who might be prompted to quit. In addition to screening for inclusion criteria, also assessed are demographics, dependence on nicotine (number of cigarettes per day and time from waking to first cigarette), smoking history (age started and previous quit attempts), and determination to quit.

#### Outcome measures

##### Primary

The proportion of people entering the smoking cessation service (that is, attending the first session of a 6-week course) over a period of 6 months from the receipt of the invitation letter. Self-reported attendance data will be validated by records of attendance at the NHS SSSs.

##### Secondary

Secondary outcome measures are: (1) 7-day point prevalent abstinence at the 6-month follow-up, validated by salivary cotinine for all participants reporting abstinence in both the Intervention and Control groups; (2) prolonged periods of abstinence of 7 days to 24 weeks measured by self-report; (3) self-reported changes in daily cigarette consumption, quit attempts, and changes in motivation and intention to quit in continuing smokers; (4) use of NRT or Zyban or Champix and other smoking cessation aids; and (5) the number completing the 6-week NHS course.

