The primary objective of the study is to assess the relative effectiveness on attendance at the NHS services of at least one session, of proactive recruitment by a brief personal letter, tailored to individual characteristics available in medical records, and invitation to a taster session to provide information about the NHS services, over a standard generic letter advertising the service.

Secondary objectives aim to: (1) assess the relative effectiveness of the two recruitment methods on biochemically validated 7-day point-prevalent abstinence rates at the 6-month follow-up; (2) compare the cost-effectiveness of the two invitation methods; (3) assess the relative effectiveness on prolonged abstinence measured by self-report of not smoking for periods of 7 days to 24 weeks at the 6-month follow-up; (4) assess the number of smokers attending the taster session and the number of smokers completing the 6-week NHS smoking cessation course; (5) assess the number of quit attempts made and any reduction in daily cigarette consumption; (6) determine predictors of attendance at the services, and of attendance at the taster sessions (in the Intervention group); (7) explore reasons for non-attendance and barriers to attendance at the NHS SSS; and (8) explore the effectiveness of the intervention by socioeconomic status, and social deprivation.

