### Evaluation procedure

Research interviewers, independent from the service providers, will conduct follow-up interviews 6 months after the date of randomisation, by telephone, to assess attendance at the services, current smoking status, daily cigarette consumption, reasons for non-attendance, and barriers to attendance in all participants. Interviewers will make a maximum of 10 attempts to contact the participant at varying times of day and on different days before classifying the participant as lost to follow-up.

All self-reported attendance at the NHS SSS will be validated by records of attendance. All participants will be asked if they attended a taster session; those answering negatively will be asked if they know or have spoken to anyone who attended a taster session. Participants claiming 7-day abstinence will be asked to provide a salivary cotinine sample to bio-chemically validate 7-day point prevalent smoking cessation at a 6-month follow-up [31]. Samples will be obtained by post using a saliva sample kit. As the cotinine content can be affected by continued use of NRT, usage at the time the sample is given will be assessed by questionnaire. A £5 Marks and Spencer voucher will be included with each kit, and a further £5 voucher sent upon return of the kit to maximise kit return [32].

Attendance at the NHS SSS could be taken up at any time during the 6 months between receipt of the invitation (Intervention Group) or standard letter (Control Group) and the 6-month follow-up. Hence, at 6 months some participants could be at varying stages of completion of a course, and at varying stages of a quit attempt. Therefore secondary outcome measures include self-reported prolonged abstinence of periods of up to 24 weeks, a measure that can also apply to those not attending the NHS service.

We will also assess 4-week abstinence in those attending the SSSs using the NHS monitoring data collected by smoking cessation advisors. These monitoring records can be used to compare quit rates of clients proactively recruited through our intervention with those of other attendees at the NHS SSSs.

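### Prolonged abstinence rests on self-report alone, so a claimant whose requested cotinine sample shows smoking still counts as a long-term quitter

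*Protocol article*

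**What the plan says.** The list of secondary outcomes in the protocol article puts two abstinence measures next to each other. The first is 7-day point prevalence at 6 months, "validated by salivary cotinine for all participants reporting abstinence in both the Intervention and Control groups". The section on changes due to additional funding later makes this measure a co-primary outcome. The second is "prolonged periods of abstinence of 7 days to 24 weeks measured by self-report", with no biochemical condition.

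The secondary objectives at the end of the Background use the same measure: "prolonged abstinence measured by self-report of not smoking for periods of 7 days to 24 weeks at the 6-month follow-up". The Evaluation procedure section does so again and gives its purpose: because participants will be at different stages of a course or a quit attempt at 6 months, the trial includes "self-reported prolonged abstinence of periods of up to 24 weeks, a measure that can also apply to those not attending the NHS service".

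On sampling, the same section says "Participants claiming 7-day abstinence will be asked to provide a salivary cotinine sample". It adds "Samples will be obtained by post using a saliva sample kit", with one voucher in the kit and "a further £5 voucher sent upon return of the kit to maximise kit return". NRT use is recorded when the sample is given, because it can affect cotinine.

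On blinding, the section on other sources of bias says "It is not possible to blind participants to the receipt of a personally tailored letter" or to the taster invitation. Follow-up interviewers are blinded to allocation.

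**The concern.** A person who reports at the 6-month interview that they have not smoked for the past 4, 12 or 24 weeks has also not smoked for the past 7 days. The protocol therefore asks that person for saliva, but the result counts only towards the 7-day outcome. A returned sample that contradicts the claim leaves the prolonged outcome unchanged.

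The person making the report knows what they were sent. Intervention participants receive a tailored risk letter from the GP, an invitation to a taster session and, if they do not attend, a repeat letter. Controls receive one generic letter. More false claims in the Intervention group are plausible, though the article has no data on this. Blinding the interviewer does not prevent it, because the report comes from the participant.

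At stake is the reading of the outcome that speaks to durable quitting. It could show a benefit that the validated outcome in the same people does not, and the plan as written does not say how to resolve the conflict.

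**Working it through.** **1. Who is asked for a sample**

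| Reported at 6 months | 7-day claimant? | Asked for cotinine? | Prolonged outcome as written |
|---|---|---|---|
| Period running to the interview | Yes | Yes | Counts, whatever the sample shows |
| Period that ended before the interview, now smoking | No | No | Unclear whether it counts |

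The wording of the objective, which ties the measure to the 6-month follow-up, favours periods that run to the interview. The outcome list gives no end point. The point below concerns the first row.

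**2. Inputs from the article:** 1,793 Control and 2,707 Intervention participants; inflation factor 1.51 for therapist clustering in the Intervention group; validated quit rates of 2.2% and 4%; 5% significance level (taken as two-sided); stated power 85.4%.

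**3. Reproducing the stated power**

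Effective Intervention n = 2,707 / 1.51 = 1,793, so 1,793 per arm.

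Power = Φ[(d − 1.96·SE0) / SE1], where d is the difference, SE0 the pooled standard error and SE1 the unpooled one.

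- d = 0.040 − 0.022 = 0.018; SE0 = 0.00579; SE1 = 0.00578.
- Without continuity correction: (0.018 − 1.96 × 0.00579) / 0.00578 = 1.15, power 87.5%.
- With 1/1,793 = 0.00056 subtracted from d: 1.05, power 85.4%, which matches the article.

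**4. What false claims could do.** The article gives no false-claim rates and no expected rates for prolonged abstinence. Assume true abstinence of 2.2% in both arms (no effect), add false claims in percentage points, and use the formula without continuity correction.

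| False claims, Intervention v Control | Observed rates | Chance of a significant result favouring Intervention, 1,793 per arm | Same, 2,707 v 1,793 |
|---|---|---|---|
| 2% v 1% | 4.2% v 3.2% | 35% | 40% |
| 1% v 0.5% | 3.2% v 2.7% | 14% | 16% |
| Equal | Equal | 2.5% (nominal) | 2.5% (nominal) |

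For the first row with 1,793 per arm: (0.010 − 1.96 × 0.00630) / 0.00630 = −0.37, and Φ(−0.37) = 35%.

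**5. Equal false claims with a true effect.** Take true rates of 2.2% and 4%, with 1% of non-abstainers in each arm claiming falsely.

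- Control: 0.022 + 0.978 × 0.01 = 3.18%.
- Intervention: 0.040 + 0.960 × 0.01 = 4.96%.
- With 1,793 per arm, power falls from 87.5% to 77.1%.

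**The case against.** Self-report here is a declared choice and partly unavoidable. Cotinine reflects recent exposure, so it can refute current abstinence but cannot confirm 12 or 24 weeks. That stands, and it is why self-report must still supply the duration. It gives no reason to ignore a result that contradicts the claim. The stated purpose of the measure, covering different stages of quitting and people who never attend the service, gives none either.

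A second objection is that rules for discordant results belong in an analysis plan, which is not shown. A fuller rule may exist there. But the article does more than stay silent: it names self-report as the measure in three places.

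Third, a bare cotinine condition could wrongly fail genuine quitters who use NRT, and unevenly so if the intervention raises attendance at services that offer NRT. This stands, and any fix must deal with it.

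Fourth, the calculations above that show inflation all assume twice as many false claims in the Intervention group, and the 2.2% base is a validated 7-day rate carried over to a different outcome. This also stands: the figures illustrate the problem and do not estimate it.

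A reader might also infer that a sample will be in hand for every claimant. The article does not support that. Claimants are asked, by post, with vouchers to encourage return, and someone whose period ended earlier is not asked at all.

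**Conclusion.** The point holds in a limited form. As written, prolonged abstinence is scored on unblinded self-report alone, and a cotinine result requested from the same person cannot overturn it. For claims that run to follow-up, this allows one participant to fail the co-primary outcome and succeed on the prolonged one.

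The direction and size of any bias are unknown. The 14-40% chances of a false positive depend wholly on assumed unequal false-claim rates; with equal rates there is no inflation, only some loss of power.

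A reader might infer that the trial's abstinence conclusion is compromised, or that the 7-day tier of this outcome is simply the co-primary outcome without validation. The first does not follow, because the co-primary abstinence outcome is cotinine-validated, interviewers are blinded and the defect sits in a secondary outcome. The second depends on reading every period as running to the interview, which the objective suggests but the outcome list does not settle. The change is worth making but is not critical to the trial.

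**What to change.** State that the prolonged period runs up to the 6-month follow-up. At each duration, count a participant as abstinent only if they report that duration and also meet the cotinine criterion used for the co-primary 7-day outcome. Handle unreturned kits and NRT users exactly as for the co-primary outcome, using the NRT information collected with the sample. Keep the self-report-only version as a supporting analysis, so that the gap between the two is visible by arm.

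The cost is revised wording and one further derived variable at each duration. No new sample or contact is needed. Reported prolonged abstinence rates will be somewhat lower.

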##### Process measures

Process measures are: (1) the number of smokers attending the taster session (Intervention group only); (2) perception of the taster session; (3) perception of the personal invitation letters; and (4) reasons for non-attendance at the taster session and barriers to attendance at the NHS services.

##### Health economic measures

The economic component will estimate the cost of providing the interventions, using primary cost data from an NHS and personal social services (PSS) perspective as recommended by National Institute for Health and Clinical Excellence (NICE) guidance [29]. We will also measure patients’ use of health and social care services using comprehensive service use questionnaires as employed on a number of other trials in the addiction field. Quality-adjusted life years (QALYs) will be calculated from the EQ-5D questionnaire [30] and combined with cost data in the cost-utility analysis.

### Evaluation procedure

Research interviewers, independent from the service providers, will conduct follow-up interviews 6 months after the date of randomisation, by telephone, to assess attendance at the services, current smoking status, daily cigarette consumption, reasons for non-attendance, and barriers to attendance in all participants. Interviewers will make a maximum of 10 attempts to contact the participant at varying times of day and on different days before classifying the participant as lost to follow-up.

All self-reported attendance at the NHS SSS will be validated by records of attendance. All participants will be asked if they attended a taster session; those answering negatively will be asked if they know or have spoken to anyone who attended a taster session. Participants claiming 7-day abstinence will be asked to provide a salivary cotinine sample to bio-chemically validate 7-day point prevalent smoking cessation at a 6-month follow-up [31]. Samples will be obtained by post using a saliva sample kit. As the cotinine content can be affected by continued use of NRT, usage at the time the sample is given will be assessed by questionnaire. A £5 Marks and Spencer voucher will be included with each kit, and a further £5 voucher sent upon return of the kit to maximise kit return [32].

Attendance at the NHS SSS could be taken up at any time during the 6 months between receipt of the invitation (Intervention Group) or standard letter (Control Group) and the 6-month follow-up. Hence, at 6 months some participants could be at varying stages of completion of a course, and at varying stages of a quit attempt. Therefore secondary outcome measures include self-reported prolonged abstinence of periods of up to 24 weeks, a measure that can also apply to those not attending the NHS service.

We will also assess 4-week abstinence in those attending the SSSs using the NHS monitoring data collected by smoking cessation advisors. These monitoring records can be used to compare quit rates of clients proactively recruited through our intervention with those of other attendees at the NHS SSSs.

We will measure perception of the personal invitation letters and of the taster session using measures from our previous trials of tailored feedback adapted to apply to the personal invitation letters [21,33]. Reasons for non-attendance at the taster session and barriers to attendance at the NHS services will be assessed using open rather than closed questions to ensure that respondents are not inhibited in their answers to those which the researchers consider to be relevant. All process measures will be included in the telephone follow-up interview 6-months after the date of randomisation. Perception of the taster session will also be assessed by an evaluation form immediately after each session.

### Sample size and power calculations

Recent evidence from the study of Murray and colleagues suggests that attendance at NHS services can be increased by 7.7% (from 8.9% to 16.6%) using a proactive intervention [18]. To detect an effect of this size at 90% power and alpha of 0.05 would require a sample of 420 participants per group. However, in the absence of other similar trials, we might assume that the uptake of services in those who receive the tailored letter and the taster session could be lower than that reported by Murray. Hence, assuming an estimated increase of 4.6% (from 8.9% to 13.5%, OR 1.65) we would require 1,029 participants per group, 2,058 in all, to detect this difference as statistically significant at the 5% level with 90% power.

Practices will be recruited from 10 different NHS SSSs. The taster sessions in each SSS will be run by the same four advisors comprising 10 therapist clusters. Thus before adjusting for clustering we would expect 103 patients per cluster. While the intervention is manualised and structured training run to reduce the variability between the interventions delivered in each SSS, to account for any persistent therapist effects that will be applied to those randomised to receive a taster session, assuming a therapist intraclass correlation coefficient (ICC) of 0.005 (in the absence of any published data), and a therapist cluster size of 103, requires further inflation of our existing sample size by a factor of 1.51 only in the Intervention group where the effects will occur. Thus, 1,554 will receive the tailored letter and taster session, 2,583 participants in total.

The same RCT [18] found validated quit rates at 6 months of 4% *versus* 2.2% (a difference of 1.8%) in the Intervention and Control Groups. With 2,583 participants (distributed between Intervention and Control groups as described above), we will be able to demonstrate a slightly larger difference of 2.2% with 80% power.

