**Method/design:**

This randomised controlled trial will recruit smokers from general practice who are motivated to quit and have not recently attended the NHS SSS. Smokers aged 16 years and over, identified from medical records in participating practices, are sent a brief screening questionnaire and cover letter from their GP. Smokers giving consent are randomised to the Control group to receive a standard generic letter advertising the local service, or to the Intervention group to receive a brief personal, tailored letter with risk information and an invitation to attend a ‘Come and Try it’ taster session. The primary outcome, assessed 6 months after the date of randomisation, is the proportion of people attending the NHS SSS for at least one session. Planned recruitment is to secure 4,500 participants, from 18 regions in England served by an NHS SSS.

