### Changes due to additional funding

As a result of the successful recruitment on the study, additional funding was approved in July 2012 to carry out additional work which will build on the study and maximise its utility. The following changes have been implemented:

(1) In addition to the original primary outcome (the proportion of people entering the smoking cessation service over a period of 6 months), 7-day point prevalent abstinence at the 6-month follow-up, validated by salivary cotinine is now also included as a co-primary outcome. This will allow us to assess whether this intervention also translates to increased quit rates, and if the quit rates in people attending as a result of this intervention differ from the usual quit rates in NHS services. This change necessitated a recalculation of the sample size needed. Assuming quit rates of 4% *versus* 2.2% in the Intervention and Control groups (mimicking the findings of Murray *et al.*[18]) an 80% increase in the sample size is required, to 1,793 in the Control group and 2,707 in the Intervention group (assuming the same therapist effect as the original protocol), a total of 4,500. A sample of this size gives 85.4% power to detect a difference of 1.8% at the 5% significance level. The same sample size would have 95% power to detect the difference between quit rates of 4.4 and 2.2% (doubling of the quit rate). Based on current recruitment figures, we estimate that an additional eight SSSs (48 GP practices) will recruit 2,060 participants, giving a total of 4,580 and meeting the requirement of the power calculation.

(2) In the pilot phase of the study we assessed barriers to attendance at the NHS services using an open question. For the remainder of the study we will use the Treatment Barriers Questionnaire, a 40-item measure of reasons for not entering smoking cessation programs that has been recently validated on a low socioeconomic population in the USA [39]. This questionnaire will allow us to assess different aspects of smokers’ decisions to attend a group or therapy session and highlight any misconceptions or lack of awareness of the service offered. It will also allow us to explore associations with demographic and dependence factors, as well as validating the questionnaire on a UK population. The Treatment Barriers questionnaire will be mailed to approximately 3,500 participants who report not attending the SSS and who agree to complete an additional questionnaire.

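### The therapist design effect of 1.51 uses the cluster size before inflation; at the planned cluster size it is about 1.75, and power for the abstinence co-primary outcome is about 83%, not 85.4%

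*Protocol article*

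**What the plan says.** Protocol article, Sample size and power calculations: 1,029 per group are needed for attendance ("from 8.9% to 13.5%, OR 1.65", 90% power, 5% level). Ten services form ten therapist clusters, which gives 103 per cluster; the section itself says this is the size before clustering is allowed for. With an ICC of 0.005, assumed because no published value was available, "a therapist cluster size of 103, requires further inflation of our existing sample size by a factor of 1.51". The factor applies to the Intervention arm only and takes it to 1,554, or 2,583 in total.

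Changes due to additional funding: validated abstinence becomes a co-primary outcome and the sample size is recalculated. The rates are "Assuming quit rates of 4% *versus* 2.2% in the Intervention and Control groups" and the sizes rise "to 1,793 in the Control group and 2,707 in the Intervention group (assuming the same therapist effect as the original protocol), a total of 4,500". Then: "A sample of this size gives 85.4% power to detect a difference of 1.8% at the 5% significance level". The same sample is said to give 95% power for 4.4% v 2.2%.

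Number of services, Abstract, Method/design: "Planned recruitment is to secure 4,500 participants, from 18 regions in England served by an NHS SSS".

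**The concern.** The factor 1.51 equals 1 + (103 − 1) × 0.005. That formula needs the number of people each advisor team will actually have in the analysis. The number of teams is fixed by the number of services, and the Intervention group section says the same advisors lead every session in a service. Inflating the arm therefore adds people to existing clusters and does not create new ones. Once the arm has grown to 1,554, the clusters hold 155 people and the factor that produced 1,554 no longer fits. The revised calculation inherits the factor.

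At stake is whether the powers printed for the abstinence co-primary outcome hold under the plan's own assumptions. A separate slip in the same section is an odds ratio that does not match the two percentages beside it.

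**Working it through.** **Inputs.** From Sample size and power calculations: ICC 0.005, 10 clusters, 8.9% v 13.5%, 1,029 per group, 1,554 Intervention. From Changes due to additional funding: 4.0% v 2.2%, 4.4% v 2.2%, 1,793 Control, 2,707 Intervention. From the Abstract: 18 services. Alpha is taken as two-sided 0.05; the article does not state sidedness, but two-sided reproduces its figures.

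**Formula.** Two proportions with pooled variance under the null and the Fleiss continuity correction. With k the ratio of Intervention to Control size and d the difference:

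- n = [1.96 √(p̄(1−p̄)(1+1/k)) + z_power √(p1(1−p1) + p2(1−p2)/k)]² / d²
- n_corrected = (n/4) [1 + √(1 + 2(1+1/k)/(n d))]²

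The Intervention size enters as its effective size, N / [1 + (m − 1) × ICC], where m is the cluster size.

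**Step 1: reproduce the plan.**

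- 8.9% v 13.5% at 90% power: n = 986, corrected 1,029 (stated 1,029).
- 1 + 102 × 0.005 = 1.51, and 1,029 × 1.51 = 1,554 (stated 1,554).
- 1,793 × 1.51 = 2,707 (stated 2,707).
- 1,793 v 2,707/1.51 = 1,793: power 85.4% for 4.0% v 2.2% (stated 85.4%) and 94.9% for 4.4% v 2.2% (stated 95%).

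The same formula without the correction gives 87.5% at the factor 1.51. So the printed 85.4% matches the corrected formula with the 1.51 deflation already in it.

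**Step 2: cluster size after inflation.**

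- Original plan: 1,554/10 = 155.4; 1 + 154.4 × 0.005 = 1.77.
- Current plan: 2,707/18 = 150.4; 1 + 149.4 × 0.005 = 1.747.
- Effective Intervention size now: 2,707/1.747 = 1,550, against the 1,793 assumed.

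**Step 3: power at 4,500 with 1,793 Control.**

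| Comparison | Formula | Factor 1.51 | Factor 1.747 |
|---|---|---|---|
| 4.0% v 2.2% | corrected | 85.4% | 82.8% |
| 4.0% v 2.2% | uncorrected | 87.5% | 85.2% |
| 4.4% v 2.2% | corrected | 94.9% | 93.3% |
| 4.4% v 2.2% | uncorrected | 95.8% | 94.5% |

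Attendance, 8.9% v 13.5%, factor 1.747, corrected formula: 98.6%.

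**Step 4: does the change to 18 services matter?** By the plan's own pre-inflation convention, 1,793/18 = 99.6 per cluster, and 1 + 98.6 × 0.005 = 1.49. Keeping 1.51 is slightly cautious on that point alone.

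**Step 5: odds ratio.** (0.135/0.865) / (0.089/0.911) = 0.1561/0.0977 = 1.60. An odds ratio of 1.65 from 8.9% would imply 13.9%.

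**The case against.** The best defence is that the shortfall is small and its level depends on the formula. The article names no continuity correction; Main analysis plans chi-squared tests and logistic regression. Without the correction, power at the right design effect is 85.2% and 94.5%, close to what is printed. This stands as a statement about the level of power. It does not rescue the calculation, because the uncorrected formula starts from 87.5% and 95.8% at the factor 1.51. The loss for 4.0% v 2.2% is 2.6 points with the correction and 2.3 without.

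Four stronger readings are tempting, and the article does not support them.

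- *Carrying the factor over to 18 services caused the shortfall.* Step 4 shows that it did not; the fault is the use of the size before inflation.
- *The original primary outcome is underpowered.* The original calculation, taken at 155 per cluster, does give 87.5% and not 90%. But that concerns 2,583 participants, a target since replaced. At 4,500 attendance has about 98.6%.
- *The trial must enrol more.* An effective Intervention arm of 1,793 over 18 clusters would take 1,793 × 0.995 / (1 − 1,793 × 0.005/18) = 3,554 people. However, the article sets no minimum power for the co-primary outcome that 82.8% would miss, and its earlier statement about quit rates was made at 80%.
- *Attrition makes this worse.* Main analysis counts those lost as still smoking, so they stay in the denominator and clusters stay as randomised. Whether the assumed quit rates already reflect that rule cannot be seen here.

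**Conclusion.** Wrong as written, and minor. The design effect of 1.51 does not match the cluster sizes that the plan itself produces. At ICC 0.005 and about 150 per service it is 1.75. By the formula that reproduces the printed figures, power at 4,500 is about 82.8% for 4.0% v 2.2% and 93.3% for 4.4% v 2.2%, in place of 85.4% and 95%. Power for 4.0% v 2.2% stays above 80% with or without the continuity correction, attendance is amply powered, and no design decision changes.

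This rests on the plan's ICC, on 18 equal clusters (unequal ones would lower power further) and on the inferred continuity correction. The ICC is an openly acknowledged assumption, so its value is not an error. As an assumed illustration with the corrected formula, 0.0025 would give 87.0% and 0.01 would give 75.1%.

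The odds ratio of 1.65 is a real slip, but 1,029 follows from the two percentages, so it feeds no other figure.

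**What to change.** - In Changes due to additional funding, compute the design effect at the planned cluster size (about 150 in 18 services, giving 1.75) and drop the carry-over of 1.51.
- Restate power for validated abstinence as about 83% for 4.0% v 2.2% and about 93% for 4.4% v 2.2%, and name the formula, including the continuity correction.
- In Sample size and power calculations, correct the odds ratio to 1.60 and note that 1.51 used the cluster size before inflation.
- Optionally, show power over a range of ICCs.

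The cost is wording only. The target of 4,500 and the analysis stay as they are; the printed power becomes slightly less favourable.
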